### Recruitment, eligibility and randomization

Participants enrolled in the trial were recruited from two sources, a program providing short-term in-home support for individuals who are medically comprised (referred to as the In-Home Support Program; IHSP) or the community at-large. IHSP provides homebound elders assistance regaining independence after illness or hospitalization through home health and homemaker services, home delivered meals, transportation, or companions but does not typically involve formal and systematic depression screening. Recruitment from IHSP involved integrating depression screening in the assessment process of participants in the program. Recruitment to the community at-large involved print media, presentations to community groups, and print media.

Eligibility criteria for BTB include being African American; ≥ 55 years of age; English speaking; cognitively intact (MMSE > 24), and a score ≥ 5 on the PHQ-9 on two sequential testing occasions. Other criteria are practical and include having a home telephone and planning to live in the area for 8 months. Individuals are not eligible with serious mental illness histories, life-limiting illnesses, involvement in another clinical depression trial, or if living in assisted living or nursing home facilities. Individuals receiving anti-depressant medications or other mental health treatments are eligible.

As individuals from IHSP may be more medically and functionally compromised than those enrolled from the community at-large, we used a stratified randomized design to assure equivalence between groups along this dimension. Permuted block randomization with each stratum (IHSP versus other recruitment source) to control for possible changes over time in subject mix was employed. The blocking number was developed by the trial senior statistician and was not disclosed to the investigative team.

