For exploratory aims, we seek to evaluate the mediational role of behavioral activation. We will use separate regressions in which the first regression will evaluate the relationship between 4 month values of the behavioral activation scale (the mediator) and symptom severity as measured by the PHQ-9 at 4 months. The second regression will evaluate the relationship between group assignment (the independent predictor variable) and symptom severity at 4-months (PHQ-9, the criterion). The third regression will evaluate the relationship of treatment assignment (predictor) to PHQ-9 severity scores (criterion) after entering behavioral activation values (mediator). To evaluate the strength of the mediation effects, we will compute the ratio of the unstandardized betas for treatment assignment (beta from regression III divided by beta from regression II) with values less than 1.00 indicating potential mediation. We will repeat these analyses using 8-month values of the PHQ-9. Another exploratory aim is to evaluate whether the intervention has a differential treatment effect based on a study participant's gender, age, or living arrangement (alone/with others), factors which have been shown to be differentially related to depression. To evaluate differential treatment effects at 4-months, we will use a similar analytic strategy as for the main effect model. ANCOVAs will be used in which the covariates will be the baseline value and specific participant characteristic (e.g., male/female; live with other or alone; age 60-64 versus 75+). We will then add an interaction term of group assignment by participant characteristic.

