### Recruitment and enrollment outcomes

Screening and enrollment results to date provide an indication of the feasibility of the BTB trial. A total of 17 senior center care managers were trained to use the PHQ-9 to screen for depression. Although screening and enrollment is closed for this trial, the screening protocol has become fully integrated into routine intake and reassessments across all senior center programs including IHSP.

A total of 703 older adults were initially screened over a 2 1/2 year recruitment period; 440 from IHSP; 263 from the community at-large (senior center members and elsewhere). Of 703, 390 (55%) scored positively (PHQ-9 ≥ 5) and were eligible for the second screen. Of 440 from IHSP, 137 (31%) were eligible for the second screen suggesting the importance of detection for this medically compromised population. Of 263 community at-large, 253 (96%) scored positively suggesting that media and outreach efforts successfully targeted individuals with depressive symptoms, individuals correctly self-identified as feeling depressed, and African Americans with depressive symptoms will volunteer for a non-pharmacological trial.

Of the initial 390 positive screens, 279 (72%) were successfully screened a second time of whom 192 (69%) were eligible and willing to participate in BTB. Another 16 individuals with initially negative PHQ-9 scores were screened 3 months later, became eligible, and enrolled in the trial for a total of 208 participants. As these participants contacted the study team prior to meeting the targeted sample size, they were included in the trial.

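### The moderator ANCOVAs leave out recruitment source, the trial's only stratification factor, and the article plans no treatment-by-source estimate (minor)

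*Protocol article*

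**What the plan says.** All references are to the protocol article.

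- **Recruitment, eligibility and randomization.** Randomisation uses permuted blocks within two strata, IHSP and other source. The reason given is: "As individuals from IHSP may be more medically and functionally compromised than those enrolled from the community at-large, we used a stratified randomized design". No other stratification factor is named. On the IHSP route, the same section says: "Recruitment from IHSP involved integrating depression screening in the assessment process of participants in the program". Community recruitment was by print media and presentations to groups.
- **Analytic plan, primary analysis.** The 4-month ANCOVA adjusts for the baseline value of the outcome and for recruitment source.
- **Aims and study hypotheses, and Analytic plan, exploratory aims.** Both name the same three moderators: gender, age and living arrangement. The exploratory paragraph says the approach will resemble that of the main-effect model, and continues: "ANCOVAs will be used in which the covariates will be the baseline value and specific participant characteristic". A group-by-characteristic interaction is then added. The examples in brackets show how the three named characteristics might be coded; they do not add a fourth.
- **Recruitment and enrollment outcomes.** "Of 440 from IHSP, 137 (31%) were eligible for the second screen", and "Of 263 community at-large, 253 (96%) scored positively". The authors take the second figure to suggest, among other things, that "individuals correctly self-identified as feeling depressed, and African Americans with depressive symptoms will volunteer for a non-pharmacological trial".

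**The concern.** There are two linked problems.

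First, the moderator models are described as similar to the primary model, but their stated covariates drop the stratification factor that the primary model keeps. The two descriptions do not match.

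Second, recruitment source is the one participant characteristic that the design singles out as likely to matter, and the article plans neither a group-by-source interaction nor a treatment effect within each source. IHSP serves homebound elders after illness or hospitalisation, so age and living arrangement may well differ between the sources. An interaction with either could then partly reflect source.

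What is at stake is the reading of the exploratory results. A listed moderator could be credited with a source difference, and a difference in effect between the two routes of entry could go unseen inside the pooled estimate.

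**Working it through.** **1. The article's own figures.** IHSP: 137/440 = 31.1%. Community: 253/263 = 96.2%. Together: (137 + 253)/(440 + 263) = 390/703 = 55.5%. All agree with the text. These are positive rates at the first screen among people screened; they do not describe the randomised groups.

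**2. The two models side by side.**

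| Model | Stated covariates |
|---|---|
| Primary ANCOVA | baseline value, recruitment source |
| Moderator ANCOVA | baseline value, participant characteristic (then group × characteristic) |

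Read literally, source is absent from the second row.

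**3. What a source covariate does and does not do.** Source as a main effect restores agreement with the primary model and the randomisation, and may gain precision. It does not separate an age interaction from a source interaction. If the treatment effect differs by source by an amount Δ, and the IHSP share differs between two age groups by δ, an apparent age interaction of δ × Δ arises whether or not source is a main effect. Illustration with assumed values: IHSP shares of 20% and 50%, effects of 0.60 SD in the community and 0 in IHSP. The subgroup effects are 0.80 × 0.60 = 0.48 and 0.50 × 0.60 = 0.30, a difference of 0.18 SD with no true age effect. Only a group-by-source term in the same model addresses this.

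**4. What pooling could hide.** With an assumed IHSP share of 137/390 = 35%, effects of 0 in IHSP and 0.60 SD in the community pool to 0.649 × 0.60 = 0.39 SD. That is almost the planned 0.40. This shows a possibility; nothing in the article indicates that it occurs.

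**5. Precision of a stratum estimate.** Inputs:
- 208 enrolled (Recruitment and enrollment outcomes) and 10% planned attrition (Analytic plan), so about 187 evaluable.
- SD 4.9 (Table 3, second-screen PHQ-9). This comes from a sample restricted to scores of 5 or more and is not a 4-month SD, so it is an approximation.
- Assumed: IHSP share 35%, range 20% to 50%; baseline-outcome correlation r from 0 to 0.6; equal allocation.

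Half-width = 1.96 × 4.9 × √(1 − r²) × √(4/n).

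| IHSP share (n) | r = 0 | r = 0.5 | r = 0.6 |
|---|---|---|---|
| 20% (37) | 3.16 | 2.73 | 2.53 |
| 35% (66) | 2.36 | 2.05 | 1.89 |
| 50% (94) | 1.98 | 1.72 | 1.58 |

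For comparison, the planned effect on this scale is 0.40 × 4.9 = 1.96 points. At a 35% share and r = 0.5, an observed effect of that size would have an interval of −0.09 to 4.01.

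**6. The interaction.** Half-width = 1.96 × 4.9 × √(1 − r²) × √(4/66 + 4/121) = 2.94 points at r = 0 and 2.55 at r = 0.5. Power to detect a 0.40 SD difference between strata is 26% at r = 0 and 37% at r = 0.6.

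**7. Comparison with a planned moderator.** Table 3 gives 22.1% men, about 41 of 187. The gender interaction has SE √(4/41.3 + 4/145.7) = 0.352 SD at r = 0, and about 20% power for a 0.40 SD difference. On the same basis, source would be no weaker than a moderator already on the list.

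**The case against.** The moderator aim is exploratory and openly unpowered. Stratification was introduced to balance the groups, and the primary ANCOVA respects it; a stratification factor need not also be tested as a moderator. The sentence before the covariate list refers back to the main model, so the missing covariate may be loose wording. An analysis plan that is not shown could add a source analysis.

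Much of this stands. It makes the point minor, and the absence of a source estimate can be asserted only for this article. It does not remove the point: the covariates are spelled out, the list conflicts with the sentence before it, and the moderators are named as the same three in two places.

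A reader might also infer more than the text supports:

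- *That the primary result is biased.* It is not; source is in that model.
- *That the trial mixes a 31%-positive group with a 96%-positive group.* Everyone enrolled was required to score at least 5 on the PHQ-9 on two occasions, and enrolment by source is not given.
- *That IHSP versus other means screen-detected versus volunteer.* The community source includes senior center members, and self-identification is offered only as a suggestion, so the proxy is imperfect.
- *That the case for routine screening rests on the IHSP stratum.* The article reports screening in all senior center programs, and its Discussion credits detection among both IHSP and community members. Its feasibility claims concern training, recruitment, enrolment and cost, not efficacy in screen-detected people.
- *That age and living-arrangement interactions are confounded by source.* No characteristics by source are reported, so this is plausible but not shown.

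**Conclusion.** The concern holds as a minor one. The stated covariates of the moderator ANCOVAs omit the sole stratification factor, against the plan's own statement that these models resemble the primary one, and the article plans no treatment-by-source estimate for the characteristic its design treats as important.

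The primary comparison is unaffected. A source-specific estimate is feasible but imprecise. Under the central assumptions the IHSP half-width is roughly the size of the planned effect (2.05 to 2.4 points against 1.96), and it is wider if the IHSP share is below 35%. These figures rest on the assumed share, correlation and attrition, and on a baseline SD standing in for the 4-month SD. Such an estimate can inform interpretation, but it should not carry a conclusion about routine screening.

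**What to change.** In the exploratory-aims paragraph of the Analytic plan:

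1. State that recruitment source is a covariate in every moderator ANCOVA, as in the primary model.
2. Add recruitment source as an exploratory moderator: fit the group-by-source interaction and report the adjusted 4-month difference with its 95% confidence interval in each stratum.
3. When interpreting an age or living-arrangement interaction, refit the model with the group-by-source term added, as a sensitivity check. The main effect of source alone does not serve this purpose.
4. State that the stratum results are descriptive, and report enrolment by source beside them.

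The cost is a few sentences of wording and one more low-powered exploratory contrast. Source was recorded at randomisation, so no new data are needed. The article says trial procedures are still in progress, so the change can be fixed before the outcome analyses.

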### Analytic plan

We based our sample size calculation on the following assumptions: a) one primary outcome (severity of depressive symptoms); b) treatment effect sizes reported in previously published intervention studies testing one or more components of the intervention we employ in BTB (effect sizes range from .70 at 6 months and .35 at 12 months in one trial^16 ^to .40 at 3 and 6 months and .60 at 12 months for another trial^14^); c) ability to detect a medium effect size of Cohen's d = 0.40; and d) type I error rate of .05 for the single primary hypothesis. A larger effect size may not be plausible, whereas a smaller effect size brings us at or near levels where the study could have statistical but not clinical significance. In order for this brief, targeted intervention to be worth implementing in a service context, it must yield more than trivial effects. Since our planned analyses are primarily analysis of covariance, we calculated the power of a two-sample t-test. Because we will use analysis of covariance to adjust for baseline values, we expect to have adequate precision and power. To attain 90% power for a two-sided alternative hypothesis using a t-test to compare the two treatment groups with respect to 4-month values require 172 study participants for an effect size of .40. We planned to recruit an additional 20 participants for a total of 192 participants (96 per group). The additional study participants allowed for a conservative estimated attrition rate of 10%. To obtain the necessary sample size of 172, we needed to enroll 192 study participants. The statistical power for secondary analyses is the same as for the primary; 90% for a 0.40 effect size with 5% two-tailed tests. Although we did not conduct power calculations for exploratory aims, these analyses are important in order to refine research questions and hypotheses worthy of future consideration, refinement of the intervention and its dissemination.

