### Sample characteristics

Participants are on average 69.5 years, mostly single, female, and with ≥ high school education. Over half (67.79%) report some to a lot of difficulty paying for basics, and have an average of 6.6 health conditions with more than a third having diabetes (42.8%), high blood pressure (78.8%), high cholesterol (58.2%), and arthritis (76.4%). Only 19.2% were on an anti-depressant medication and 16.8% on an anti-anxiety medication whereas 52.9% were on pain medications. The average second PHQ-9 score was 13 with 72% reporting moderate to severe symptoms. (Table 3)

**Table 3 T3:** Baseline Characteristics of BTB Sample (N = 208)

Characteristic	Mean (SD)	%
Age^a^	69.5 (8.7)	
Sex		
Male		22.1
Female		77.9
Education		
< HS		21.2
HS/GED		29.3
> HS		49.5
Paying for basics		
Not difficult at all		19.7
Not very difficult		12.5
Somewhat difficult		37.5
Very difficulty		30.3
Marital status		
Single		88.0
Married		12.0
Number of health conditions	6.6 (3.5)	
Antidepressant medication		19.2
Anxiety medication		16.8
Pain medication		52.9
PHQ9 Score (second screen)	13.0 (4.9)	
Minimal/no depression (0-4)		0.0
Mild depression (5-9)		28.5
Moderate depression (10-14)		35.3
Moderate/severe depression (15-19)		24.2
Severe depression (≥ 20)		12.0

^a^N = 207.

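### The example age bands for the exploratory moderator test (60-64 versus 75+) do not match eligibility from age 55 and, taken literally, leave out ages 55-59 and 65-74

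*Protocol article*

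**What the plan says.** - **Aim.** The Analytic plan sets out to look for a "differential treatment effect based on a study participant's gender, age, or living arrangement (alone/with others"). Neither this section nor Aims and study hypotheses restricts the ages to which the question applies.
- **Model.** The moderator models are ANCOVAs, described as similar in strategy to the main model, with the baseline value and the participant characteristic as covariates. The test is the interaction: "We will then add an interaction term of group assignment by participant characteristic".
- **Coding.** A bracketed list of examples gives male/female, then "live with other or alone; age 60-64 versus 75", with a plus sign after the 75. No other age coding appears in the article.
- **Eligibility.** Recruitment, eligibility and randomization sets the lower limit at "≥ 55 years of age" and states no upper limit.
- **Sample.** Sample characteristics reports "Participants are on average 69.5 years". Table 3 gives mean (SD) 69.5 (8.7), with age known for 207 of 208, and no counts by age band.
- **Status.** The analysis is exploratory: "Although we did not conduct power calculations for exploratory aims".

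**The concern.** Two of the three example codings, sex and living arrangement, place every participant in a group. The age coding does not. Someone aged 57 or 70 is eligible and enrolled but belongs to neither band, and the article does not say how such people are handled. An analyst following the text would have to drop them or invent a rule after the data are in.

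Two things are at stake. The age question would be answered without the ages around the centre of the sample, and the interaction would be estimated less precisely than the collected data allow. The article wants the exploratory analyses to show whether some groups benefit more than others and to help refine the intervention. A test that is silent on ages 65-74 serves that purpose poorly.

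A smaller point lies in the same paragraph. The main ANCOVA includes recruitment source, the stratification variable; the covariates listed for the moderator models do not name it.

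**Working it through.** The plan states no figure for the age subgroups, so there is none to reproduce. The mismatch needs no arithmetic; its size does.

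**1. Coverage.** Eligible ages are 55 and over. The bands cover 60-64 and 75+. The gaps are 55-59 and 65-74, and 69.5 falls in the second.

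**2. Share left out.** Inputs from Table 3: mean 69.5, SD 8.7, N = 207. The shape is an assumption. Each distribution below is restricted to ages 55 and over; all but the first are matched to that mean and SD.

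| Assumed shape | 55-59 | 60-64 | 65-74 | 75+ | Left out |
|---|---|---|---|---|---|
| Normal (69.5, 8.7) cut at 55 | 9.4% | 17.3% | 45.6% | 27.7% | 55.0% (114) |
| Truncated normal, matched | 14.7% | 19.7% | 39.9% | 25.7% | 54.6% (113) |
| Shifted gamma | 9.8% | 25.5% | 42.4% | 22.3% | 52.2% (108) |
| Scaled beta | 14.4% | 21.5% | 38.0% | 26.2% | 52.3% (108) |
| Shifted lognormal | 5.0% | 29.7% | 45.7% | 19.6% | 50.7% (105) |

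Using a mean of 70.0, to allow for age in completed years, gives 51-54%. The sampling SE of such a share is about √(0.5 × 0.5 / 207) = 3.5 percentage points. Mean and SD alone do not fix the share: over ages 55 to 100 the mathematical bounds are 0% and 99%.

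**3. Detectable interaction.** Matched truncated normal, 1:1 arms, outcome SD = 1, two-sided 5%, 80% power. With age groups of size a and b, SE = √(4/a + 4/b), and the detectable interaction is (1.96 + 0.84) × SE.

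- *60-64 versus 75+:* a = 207 × 0.197 = 40.8 and b = 207 × 0.257 = 53.2. SE = √(4/40.8 + 4/53.2) = 0.416. Detectable: 1.17 SD.
- *55-74 versus 75+:* a = 153.8, b = 53.2. SE = 0.318. Detectable: 0.89 SD.
- *Linear group × age, all 207:* SE per SD of age = 2/√207 = 0.139. The mean ages in the two quoted bands are about 62.6 and 81.2, so the same contrast spans 18.6/8.7 = 2.14 SD of age. SE = 0.139 × 2.14 = 0.297. Detectable: 0.83 SD.

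For the same contrast, the two-band estimate has (0.416/0.297)² ≈ 1.96 times the variance of the linear term.

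**4. Like-for-like comparison.** The 0.89 SD refers to a narrower age contrast, because the mean age in 55-74 is about 65.5. If moderation is linear, years of age contrast per unit SE are 18.6/0.416 ≈ 44.6 for the quoted bands, 15.7/0.318 ≈ 49.3 for 55-74 versus 75+, and 8.7/0.139 ≈ 62.6 for continuous age. The quoted bands thus lose about 10% against the covering split and about 29% against continuous age.

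**The case against.** **It is only an example.** The bands follow an e.g. in a condensed article, and detailed coding may sit in an analysis plan that is not shown. This stands in part. A reader might infer that the plan has decided to discard the middle ages; the article does not say so, and the aim carries no age restriction. But the bracket gives a coding for each of the three moderators named, and its age entry contradicts the article's own eligibility rule. That is a conflicting statement, not an omitted detail.

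**It may be a slip**, for example for 60-74. That is possible and cannot be settled from the article. That version would still omit ages 55-59, about 15% under the truncated normal, with a detectable interaction of about 0.92 SD.

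**The share is not a document figure.** This stands. A reader might state as fact that over half the sample is lost. Table 3 does not support that; roughly half, under an assumed shape, is what can be said.

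**Separated bands widen the age contrast.** This also stands: against a covering two-group split the loss is modest, about 10% under linear moderation. The larger gain needs continuous age and its linearity assumption.

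**The analysis is exploratory and unpowered.** True, and it limits the weight of the point. The error rate in the plan is set as a "type I error rate of .05 for the single primary hypothesis", which this does not touch.

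**Recruitment source may be implied.** Calling the strategy similar to the main model can be read as keeping it, so this is a request for clarity and not an error shown.

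**Conclusion.** The point holds as a mismatch between the example age bands and the eligibility criterion, in an exploratory analysis. Read literally, the coding omits ages 55-59 and 65-74, including the band that holds the mean age; this rests on no assumption.

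The size does rest on assumptions. Under common distribution shapes with the reported mean and SD, about 51-55% of the 207 participants with recorded age (about 105-114 people) would be left out. Under the matched truncated normal, the interaction detectable with 80% power is about 1.17 SD, against about 0.83 SD for a linear term over the same contrast. Those figures use all 207. With 172 analysed, the analysis number in the sample size calculation, the two-band figure rises to about 1.28 SD.

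The primary 4-month comparison is unaffected. A reader should not infer that the plan definitely drops these participants, or that the trial's main conclusions are at risk.

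**What to change.** Replace the age example with one of the following:

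- **Preferred:** age as a continuous, centred moderator (group × age) in all participants with recorded age, with the main effect of age in the model and a check of linearity, for example with a spline.
- **Alternative:** bands covering every eligible age, for example 55-64, 65-74 and 75+. These also suit display of the continuous result.

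State as well that recruitment source is kept as a covariate in all the moderator models, as in the main ANCOVA.

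This costs a line or two in the analysis plan and no new data. Enrolment is closed, but trial procedures are in progress and results are still to be reported, so the change can be made before the analysis. The downside of the preferred option is its linearity assumption, which must be checked.
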